## Abstract

Background: Deep Brain Stimulation (DBS) of the sensory thalamus has been proposed for 40 years to treat medically refractory neuropathic pain, but its efficacy remains partial and unpredictable. Recent pilot studies of DBS targeting the ACC, a brain region involved in the integration of the affective, emotional, and cognitive aspects of pain, may improve patients suffering from refractory chronic pain. ACC-DBS could be complementary to thalamic DBS to treat both the sensory-discriminative and the affective components of chronic pain, but the safety of combined DBS, especially on cognition and affects, has not been studied. Methods: We propose a prospective, randomized, double-blind, and bicentric study to evaluate the feasibility and safety of bilateral ACC-DBS combined with unilateral thalamic DBS in adult patients suffering from chronic unilateral neuropathic pain, refractory to medical treatment. After a study period of six months, there is a cross-over randomized phase to compare the efficacy (evaluated by pain intensity and quality of life) and safety (evaluated by repeated neurological examination, psychiatric assessment, cognitive assessment, and assessment of affective functions) of combined ACC-thalamic DBS and thalamic DBS only, respectively. Discussion: The EMOPAIN study will show if ACC-DBS is a safe and effective therapy for patients suffering from chronic unilateral neuropathic pain, refractory to medical treatment. The design of the study will, for the first time, assess the efficacy of ACC-DBS combined with thalamic DBS in a blinded way.

## 1. Introduction

Deep brain stimulation (DBS) has been proposed since the 1970s to treat refractory chronic pain using two intracerebral targets: the sensory thalamus and the periaqueductal and periventricular grey matter [1,2]. The latter target was recommended for nociceptive, although DBS of the sensory thalamus has been rather used for refractory neuropathic pain. Thalamic DBS targeted the ventral posteromedial (VPM) and ventral posterolateral (VPL) nuclei, the site of pathological neuronal hyperactivity secondary to deafferentation [3,4]. DBS for pain was commonly practiced in the 1980s and 1990s, and its results have been reported in numerous case series (reviewed in [5,6,7]). In the case of neuropathic pain (mainly facial neuropathic pain and post plexus avulsion pain), reported thalamic-DBS efficacy varied from 40% to 60% in published studies; efficacy is usually defined as pain improvement > 50%. However, thalamic DBS has been used less since the emergence of cortical stimulation, and several studies report partial, insufficient, or short-lasting efficacy [8].

Recently, the anterior and dorsal cingulate gyrus has been proposed as a novel target for DBS for refractory pain [9]. The anterior cingulate gyrus (ACC) is located on the medial side of the frontal lobe, around the corpus callosum. It can be functionally and histologically distinguished into its dorsal part (Brodman’s area 24), located above the corpus callosum (CC), its rostral part (area 32), anterior to the CC, and its subgenual part (area 25), located below the knee of the CC. The dorsal anterior cingulate plays a functional role in motivation and affect management. The cingulate belongs to the Pain Matrix, a set of cortico-subcortical regions activated during pain processes [10]. Functional brain imaging studies suggest that the anterior cingulate is involved in the management of the cognitive, emotional, and affective components of pain (reviewed in [10,11]. In particular, the ACC is thought to be involved in the process of attributing unpleasantness or “suffering” to the experience of pain perception.

The dorsal ACC has been used as a target for the neurosurgical treatment of chronic pain, especially by performing focal lesions called cingulotomies. Case series report variable efficacy, around 50% improvement [12,13]. Patients treated by cingulotomy reported a dissociation between the persistence of the usual pain perception and a certain indifference to pain linked to the loss of perception of its unpleasant aspect. The main adverse effect of cingulotomy was apathy, although its incidence is unclear.

Therefore, chronic electrical stimulation of the ACC (DBS-ACC), a non-invasive and reversible technique, was proposed as an alternative to cingulotomy. First, in an isolated case [14], and more recently, in a series of 16 patients with refractory neuropathic pain [15], the DBS leads were implanted in the same region of the ACC that was previously targeted for lesions. In this series, DBS-ACC treatment induced a reduction of pain intensity below a VAS score of 4/10 in one-third of the patients. The overall health status (EQ-5D) and quality of life (SF-36) of the 16 treated patients improved significantly (respectively, by 20% and 7%) after ACC-DBS at a mean follow-up of 13 months. Improvement of quality of life in patients who had no change in pain intensity suggests that DBS-ACC may induce changes in the cognitive and emotional integration of pain, as if the patients had become partially indifferent to their pain, as some patients spontaneously reported [15].

DBS of the anterior cingulate (DBS-ACC) appears to be an innovative and hopeful approach for the treatment of patients with severe chronic pain resistant to all other treatments. However, these encouraging preliminary data from DBS ACC on a small number of patients need to be confirmed by a prospective study. Moreover, the ACC is involved in many cognitive and emotional processes. These functions have not been studied in patients treated with chronic ACC stimulation. Furthermore, one may fear that indifference to pain, a therapeutic effect sought and reported by ACC-DBS patients, may be associated with an emotional indifference (anhedonia) extended to other domains and/or with a loss of motivation (apathy) which may have an impact on patients’ lives. An evaluation of the cognitive, emotional, and affective consequences of DBS-ACC appears to be essential before going further in its therapeutic development.

Finally, the place of ACC-DBS in relation to thalamic-DBS remains to be clarified. In the study by Boccard et al., 7 out of 16 patients had been previously treated unsuccessfully with thalamic or periaqueductal DBS, and DBS-ACC was therefore presented as an alternative to “classic” DBS. However, these two DBS modalities have different mechanisms of action. Thalamic DBS is supposed to modulate the transmission of the nociceptive message and inhibit the pathological hyperactivity of deafferented neurons, which tends to reduce the intensity of the pain. ACC-DBS would act (under reserve of the data available) by modulating the emotional integration of pain at the level of the ACC without modifying the intensity and the perception of pain. Because of their different mechanisms of action, these two techniques could be complementary or even synergistic, acting on several dimensions of chronic pain and its perception.

To answer these questions, we propose an exploratory study evaluating the feasibility and tolerance of an approach combining ACC-DBS and thalamic-DBS in patients with severe chronic neuropathic pain for which all other therapeutic alternatives have failed. This trial will systematically investigate the possible cognitive, emotional, and affective consequences of DBS-ACC.

All patients will be treated with active and adjusted thalamic DBS for the duration of the study in order to provide a validated and potentially effective therapeutic solution. In case of poor tolerance of the thalamic stimulation, it will be stopped. The study will include a randomized phase during which ACC-DBS will be alternatively active or inactive in order to evaluate its effects in a comparative way. The lack of sensation of DBS-ACC will allow its evaluation in a double-blind phase. We will not include patients presenting with post-stroke pain in this study in order to ensure the structural integrity of the neural networks that potentially support the mechanism(s) of action of ACC-DBS. We will not include patients who respond to rTMS and, therefore, potentially respond to cortical stimulation, a technique considered less invasive than DBS.

## 2. Methods and Design

### 2.1. Study Design

The EMOPAIN study is a bicentric prospective, feasibility, and safety study to evaluate bilateral ACC-DBS combined with unilateral thalamic DBS in patients suffering from refractory chronic unilateral pain. The study design is summarized in Figure 1. The total duration of the study will be 23 months.

All patients will be treated with DBS-thalamic, activated one day after surgery and remaining active for the duration of the study in order to provide a validated and potentially effective therapeutic solution. ACC-DBS will be activated 1 month after surgery (M1), and parameter settings will be optimized during the next 3 months (M1–M4).

In order to evaluate the efficacy and safety of ACC-DBS, the study will also include a randomized phase during which DBS-ACC will be alternatively active or inactive. The lack of sensation induced by DBS-ACC will allow its double-blind evaluation. Randomization will take place 4 months after the surgery (Figure 1). The aim of the randomized phase is to compare the combination of DBS-ACC and DBS-thalamic with DBS-thalamic alone, with the patient as his own control, in two 3-month periods organized in a cross-over design. The thalamic stimulation will be left on throughout this phase. The patient will be randomized (centralized randomization) between a DBS-ACC sequence on (“On”) and a DBS-ACC sequence off (“Off”), these parameters being set by the neurosurgeon. Patients and evaluating neurologists will be blinded for the results of randomization. The two sequences will be separated by a two-week wash-out period to avoid a residual effect. Evaluation data will be collected by the neurologist at the end of each sequence (M7 and M10).

### 2.2. Endpoints

The feasibility of ACC-DBS will be evaluated by the proportion of patients undergoing with success the process of surgical intervention, chronic stimulation, and evaluation without serious adverse events. Safety will be evaluated by repeated general and neurological examination, psychiatric assessment, and assessment of cognitive and affective functioning. The global cognitive assessment includes mini mental status (MMSE), the French version of the Free and Cued Selective Reminding Test (FCSRT), the GREFEX battery, including the Trail Making Test (TMT) [16], the Stroop test, the six elements test, the Brixton test, the double task, the modified card sorting test (MCST), and verbal fluencies [17], and the Digit Span and Digit Symbol-coding (WAIS IV) [18]. Assessment of affective functions will be performed using the Hospital Anxiety and Depression (HAD) scale, the Lille Apathy rating scale (LARS), the revised version of the “Reading the mind in the eyes” test [19], the Facial Expressions of Emotion—Stimuli and Tests (FEEST) scale [20], and the Multidimensional Assessment of Thymic States [21].

DBS efficacy will be evaluated using pain intensity on the Visual Analogic Scale (VAS), Brief Pain Inventory, McGill Pain Questionnaire, Patients’ Global Impression of Change (PGIC), and quality of life improvement (EQ-5D-3L health questionnaire).

Assessments will be performed 1 month before surgery and 1, 4, 7, 10, and 22 months after.

### 2.3. Patients

We will include 10 adult patients (age 18–70 years old) suffering from chronic (duration > 1 year) unilateral neuropathic pain, severe (VAS score > 6/10), with high emotional impact (HAD sub-scores > 10), considered resistant to medication specific to neuropathic pain at sufficient doses and durations (including at least antiepileptics and antidepressants), and not sufficiently improved by rTMS and relevant surgical solutions. Patients who respond to rTMS will not be included as they may potentially respond to cortical stimulation, a technique considered to be less invasive than DBS.

Non-inclusion criteria will be cognitive impairment (MMSE score < 24), DSMIV axis I psychiatric disorder, and contra-indication to surgery, DBS, anesthesia, or MRI.

Considering the pioneering nature of this study and the number of patients required in similar pilot studies exploring the effects of DBS in emerging indications, it seems to us that 10 patients would be sufficient to achieve the objectives of this project.

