### 3.3. Statistical Analysis

Given the preliminary nature of this study, the analysis of the data concerning the efficacy of this approach will be essentially descriptive and will concern the evolution of the scores of the pain scales and neuropsychological scales over time. The results will be expressed in the form of individual graphical curves showing the evolution of these scores. These curves will make it possible to compare this evolution before and after stimulation.

The tolerance and efficacy of the combined DBS-ACC and thalamic DBS will be evaluated by comparing the postoperative scores at M22 with the preoperative scores (“baseline”). The tolerance and efficacy of DBS-ACC will be assessed by comparing the scores of each of the randomized sequences DBS-ACC “On” and DBS-ACC “Off”. Due to the small number of subjects in this study, statistical analysis will be based on non-parametric tests.

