However, it is possible that certain pain etiologies may respond better to ACC-DBS than others. In our study, the pathophysiology of pain will be relatively homogenous; only patients with chronic refractory neuropathic pain will be included. We will not include patients with post-stroke pain in this study to ensure the structural integrity of the neural networks that potentially support the DBS-ACC mechanism(s) of action.

We expect DBS-ACC to be successful in chronic and refractory neuropathic pain and to be well tolerated. We expect that its effect on the emotional and affective components of pain will not be accompanied by undesirable consequences on the overall cognitive, affective, and emotional functioning of patients. This would confirm the interest in DBS-ACC as a potential alternative or complement to DBS-thalamic and would offer refractory chronic pain patients a new therapeutic option.

This study will also allow the collecting of data for the construction of a larger study.

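### A 10-patient exploratory study with difference tests cannot show that ACC-DBS is safe and effective, as the abstract promises; restate the claim and report tolerance as estimates with intervals

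*Protocol article*

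**What the plan says.** The Introduction sets an exploratory aim: "we propose an exploratory study evaluating the feasibility and tolerance of an approach combining ACC-DBS and thalamic-DBS". Section 2.1 likewise calls the trial a feasibility and safety study.

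Section 2.3 fixes the size at 10. It cites the pioneering nature of the work and "the number of patients required in similar pilot studies exploring the effects of DBS in emerging indications", and concludes that "it seems to us that 10 patients would be sufficient to achieve the objectives of this project". It gives no effect size, SD, significance level, power, margin or precision target.

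The abstract goes further: "The EMOPAIN study will show if ACC-DBS is a safe and effective therapy".

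Section 3.3 plans two tolerance comparisons, both within patients. For the combined treatment, tolerance is "evaluated by comparing the postoperative scores at M22 with the preoperative scores". For ACC-DBS itself, scores in the On sequence are compared with scores in the Off sequence. On method it says: "Due to the small number of subjects in this study, statistical analysis will be based on non-parametric tests". The same section describes the efficacy analysis as mainly descriptive, with individual curves for both the pain and the neuropsychological scales.

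Section 2.2 adds clinical, neurological and psychiatric examinations, and the proportion of patients who complete the process free of serious adverse events. No threshold is attached to that proportion.

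The Discussion expects that the effect of ACC-DBS on the emotional side of pain "will not be accompanied by undesirable consequences on the overall cognitive, affective, and emotional functioning of patients", and foresees a larger study.

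**The concern.** Tolerance is the central question. The Introduction names apathy and emotional indifference as the harms to fear, and treats their evaluation as a condition for further development. The score comparisons that address these harms are tests for a difference, while the result the sponsor hopes for is the absence of one. In that situation a small sample makes the hoped-for result more likely whether or not harm exists.

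A reader who has been told that the study will show safety, and that 10 patients are enough, could take a run of non-significant cognitive and affective scores as that demonstration. What is at stake is the conclusion that may be drawn, and so the basis on which a larger trial would be planned. The choice of 10 patients for a pilot is not itself in question.

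**Working it through.** **The plan's own figure.** The sample size of 10 rests on precedent. With no inputs stated, it can be neither reproduced nor refuted. The check is therefore what 10 patients can show.

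**Assumptions (none is in the document).** Two-sided 5% level; exact Wilcoxon signed-rank test; normally distributed paired differences; effects in SDs of the paired difference.

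**1. Power to detect a decline.** With n = 10 the test rejects when the smaller rank sum is at most 8, an actual level of 50/1024 = 0.0488. Simulation (40,000 runs) gives:

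| True decline (SD of paired difference) | Power, n = 10 | Chance of a non-significant result |
|---|---|---|
| 0.3 | 13% | 87% |
| 0.5 | 28% | 72% |
| 0.8 | 60% | 40% |
| 1.0 | 79% | 21% |

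If only 8 patients were evaluable (illustrative), power would be 19%, 43% and 61% at 0.5, 0.8 and 1.0 SD. The effect detectable with 80% power at n = 10 is about 1.0 SD (paired t: 0.996).

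**2. Sensitivity to the meaning of SD.** If the decline is expressed in between-patient SDs, then SD of the difference = SD × √(2(1 − ρ)), with ρ the within-patient correlation.
- ρ = 0.5: √1.0 = 1, so 0.5 SD stays 0.5, with power about 28%.
- ρ = 0.8: √0.4 = 0.632, so 0.5/0.632 = 0.79, with power about 60%.

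A decline of 0.5 between-patient SD thus has power of about 28% to 60% over this assumed range.

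**3. Precision.** By the t approximation, the half-width of a 95% interval for the mean paired difference is t(0.975; 9)/√10 = 2.262/3.162 = 0.72 SD. If there is truly no difference, the smallest margin that can be excluded with 80% power is about 0.85 SD (one-sided 5%) or 1.00 SD (one-sided 2.5%).

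**4. Serious adverse events.**
- Upper limit after 0/10: 1 − 0.05^(1/10) = 25.9% (one-sided 95%), or 1 − 0.025^(1/10) = 30.8% (two-sided 95%).
- Chance of seeing no event: 0.9^10 = 35% if the true rate is 10%, and 0.8^10 = 11% if it is 20%.
- Completion free of serious events, Clopper-Pearson 95% interval: 10/10 gives 69% to 100%; 8/10 gives 44% to 97%.

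**The case against.** The strongest reply is that this is a declared pilot and is being read as a confirmatory trial. Size by precedent is ordinary for such a study, the sufficiency sentence is hedged, and the Discussion points to a larger trial. Section 3.3 presents the analysis as mainly descriptive, and its individual curves include the neuropsychological scales. Safety also draws on examinations and on the proportion free of serious events. The Discussion's sentence on undesirable consequences is an expectation and sets no success criterion. Interval methods can be left to an analysis plan that is not shown.

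Much of this stands. In particular, a reader might infer that the plan will declare ACC-DBS safe when a test is non-significant. No section states such a rule, so that reading is not supported. Nor do the documents support saying that 10 patients is the wrong number for the exploratory aim, or that safety rests on tests alone.

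Two things remain. The abstract's promise is an affirmative statement that no analysis plan can make true with 10 patients. And section 3.3 words its descriptive caveat for efficacy, then applies comparisons and tests to tolerance with no criterion for reading a null result. The examinations and the event-free proportion do not close that gap: they have no threshold, and the proportion is imprecise even at 10/10.

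A formal rule with a harm threshold for every scale would be hard to defend here. Section 2.2 lists more than a dozen instruments. By symmetry with the power figures, a 95% interval from 10 patients would exclude a 0.5 SD harm only about 28% of the time when there is truly none.

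**Conclusion.** The point holds as a mismatch between the size of the study and the conclusion promised for it. With 10 patients, a true decline of 0.5 SD of the paired difference would be non-significant about 72% of the time. A clean serious-event record would still be compatible with true rates up to about 26% to 31%. The study can give preliminary estimates; it cannot establish safety or efficacy.

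The power figures rest on an assumed two-sided 5% level, normal paired differences and illustrative effect sizes. Power stays between 13% and 60% for declines of 0.3 to 0.8 SD of the difference, so the conclusion does not depend on one choice. The event limits need only the number of patients and the confidence level. That a null test would be taken as proof of safety is a risk left open by the wording and is not something the plan states.

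**What to change.** Keep 10 patients and make two changes.

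1. **Abstract and section 2.3.** Say that the study gives preliminary estimates of feasibility, tolerance and effect, and that it cannot confirm safety or efficacy. Limit the sufficiency statement to that purpose.
2. **Section 3.3.** Beside the individual curves, report the On–Off and M22–baseline differences on the safety scales as estimates with exact 95% confidence intervals, for example the Hodges-Lehmann estimate with the interval from the signed-rank test. Give the proportion free of serious adverse events with an exact interval. State that a non-significant difference is not evidence of tolerance.

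A pre-stated harm threshold for a scale is optional.

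The cost is wording, slightly more analysis and a less favourable stated conclusion. Visits, procedures and sample size do not change, and the larger study would inherit usable estimates.

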### 2.4. Ethicals Considerations

The design of the study has been approved by the Ethical Medical Committee (“Comité de Protection de Personnes Sud Meditteranée”, 2017). Informed consent will be obtained from all patients before inclusion. There will be no financial reward for the patients.

### 2.5. Interventions

The day before the operation, a morphological brain MRI, including diffusion tensor imaging (DTI) sequence, will be performed on a 3 Tesla MRI in order to obtain high-quality brain images, guaranteeing quality surgical targeting.

The operation consists of the unilateral lead implantation in the sensory thalamus contralateral to the pain side, combined with bilateral lead implantation in the dorsal anterior cingulate gyrus. These electrodes will then be connected by subcutaneous cables to two abdominal or pectoral subcutaneous generators: one for the thalamic stimulation, the other for the cingulate stimulation.

The stereotactic implantation technique will be similar to the technique already used for DBS in movement disorders and other conditions. Similar to what may be used in Parkinson’s disease, this operation will be performed under local anesthesia and will include a phase of intraoperative micro-electrode recording and “test” stimulation in order to optimize the implantation of the thalamic lead within the sensory thalamic nuclei.

